## Statistical analysis

4

The datasets included in the statistical analyses will be divided into the Full analysis set (FAS) and the Per Protocol Set (PPS). FAS refers to people who have had at least one follow-up after enrollment and have data on key indicators. Cases missing baseline data for the primary evaluation indicator will be excluded. PPS refers to cases that meet the inclusion and exclusion criteria on the basis of FAS, have valid baseline values, have good adherence, and do not violate the clinical study protocol. Data will be analyzed using both the FAS and the PPS, with FAS results being the mainstay.

Statistical tests will be performed using SPSS version 23.0 software and relevant data will be considered statistically significant if P < 0.05. Comparisons between groups will be made using chi-square analysis, continuous variables will be statistically described using mean ± standard deviation (M ± SD), comparisons between the two groups will be made using the independent samples t-test, and repeated measures such as ANOVA will also be used to compare the degree of symptomatic improvement in the intervention group and the control group and to analyze the group × time interaction. In addition, Binary Logistics regression and COX regression will be used to compare the changes in each indicator before and after the intervention between the two groups. Multiple imputation will be used for handling missing data.

Data will be analyzed using content analysis to extract patients’ experiences of using the Smart CBT-I plus. The audio recordings of the semi-sectional constructed interviews will be transcribed into text before the interview data is independently coded and analyzed by each of the 2 researchers, and if inconsistencies are encountered, they will be discussed to reach consistent conclusions, and inter-researcher coding consistency will be used to rate the study’s reliability.

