### Participant timeline

2.6

At baseline and at the end of the intervention, patients will be subjected to a series of psychological assessments, including sleep and mood symptoms. For patients in the study group, at the end of the 35-day intervention, a random sample of 30 patients will also be given a one-on-one qualitative interview to discuss their experience with Smart CBT-I plus, the interview results will be recorded. All patients will be evaluated at follow-up at 6 and 12 months after completion of treatment. Patients will be made aware of all assessment results. They will also be able to view their weekly assessments on their own in the program. they will still be able to use the program on their own after the 35-day session. The specific follow-up schedule is shown in **Table 1**.

**Table 1 T1:** Subject visit schedule.

items	Screening visit	Baseline visit	Post-intervention visit	Follow-up visit	
Visit	V0	V1	V2	V3	V4
Time	Day -7-0 * (± 1 day)	Day 0 (± 1 day)	35 days after baseline (± 3 days)	6 months after intervention (± 7 days)	12 months after intervention (± 7 days)
Sign informed consent	**×**				
Inclusion/exclusion criteria	**×**	**×**			
Self-made general demographic questionnaire		**×**			
Self-made clinical feature collection scale		**×**			
Semi-structured sleep assessment questionnaire		**×**			
Insomnia Severity Index Scale (ISI)	**×**	**×**	**×**	**×**	**×**
Hamilton Depression Scale (HAMD)	**×**	**×**	**×**	**×**	**×**
Hamilton Anxiety Scale (HAMA)	**×**	**×**	**×**	**×**	**×**
Clinical Gross Impression Scale (CGI)		**×**	**×**	**×**	**×**
Epworth Sleepiness Scale (ESS)		**×**	**×**	**×**	**×**
Pittsburgh Sleep Quality Index Scale (PSQI)		**×**	**×**	**×**	**×**
Hygiene economics evaluation		**×**	**×**	**×**	**×**
Adverse event report form			**×**	**×**	**×**
Serious Adverse Event (SAE) report form			**×**	**×**	**×**
Six quality of life questionnaires		**×**	**×**	**×**	**×**
Generalized Anxiety Scale (GAD-7)		**×**	**×**	**×**	**×**
Dysfunctional Beliefs and Attitudes about Sleep Scale (DBAS-16)		**×**	**×**	**×**	**×**
Rapid Report of Depressive Symptoms - Self-report score 16 items (QIDS-SR16)		**×**	**×**	**×**	**×**
Life Event Scale (LES)		**×**			
Therapeutic Alliance Questionnaire Revision (WAI-S)			** *×* **		
Outline of semi-structured qualitative interviews (30 patients of study group)			** *×* **		
medication administration record	**×**	**×**	**×**	**×**	**×**

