## Outcome measurements and instruments

3

This study will use both self-assessment and other-assessment scales, and the study assessments will be completed partly by the patients online in self-help and partly with the help of an assessor. Analyses of these scales will be conducted by a statistician without knowing how the patient groups will be assigned.

The efficacy evaluation indicators include (1) Main indicators:

Between-group comparison of ISI scores between the two groups after intervention and within-group comparisons before and after the intervention.

The ISI is a brief sleep self-assessment tool with 7 items to evaluate the severity of a patient’s insomnia (38). Using a single-item scale from 0 to 3, it is primarily used to evaluate the severity of insomnia in patients. The ISI is highly sensitive, valid, reliable, brief, easy to administer, statistically easy to use, provides relevant information for diagnosis and treatment, and is a reliable tool for quantifying the perceived severity of insomnia. The intervention will be considered successful when, after 35 days, a significant difference in the ISI scores between groups is found in the study group compared to the control group. Also, within-group comparisons between the two groups before and after the intervention will be explored thereby confirming the effect of the intervention more clearly.

(2) Secondary indicators:

a. Between-group comparison of the total HAMA score reduction rate in the two groups of patients;

b. Between-group comparison of the HAMD total score reduction rate in the two groups of patients;

The HAMA (39)and HAMD (40, 41) are scales that measure the severity of anxiety and depressive symptoms and are considered to be among the most widely used scales with good reliability and validity in the measurement of anxiety and depression. The HAMA contains 14 items and the HAMD contains 17 items, most of which are scored on a 4-point scale (from 0 to 4).

c. between-group comparison of sleep latency reduction time before and after intervention in the two groups of patients;

d. intergroup comparison of the time of increase in total sleep duration before and after intervention in the two groups of patients;

e. Comparison between the two groups of patients before and after the intervention of the Pittsburgh Sleep Quality Index (PSQI) total score reduction rate and the change of each factor score;

(3) Other psychological scales:

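### The day-35 ISI comparison should have one named, baseline-adjusted primary analysis; logistic and Cox regression do not fit changes in scores

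*Protocol article*

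**What the plan says.** Under Outcome measurements and instruments, the main indicator is "Between-group comparison of ISI scores between the two groups after intervention and within-group comparisons before and after the intervention". The success rule is: "The intervention will be considered successful when, after 35 days, a significant difference in the ISI scores between groups is found". No test is named there.

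Under Statistical analysis, the methods are listed for the outcomes in general:

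- "comparisons between the two groups will be made using the independent samples t-test, and repeated measures such as ANOVA will also be used". The stated purpose of the repeated-measures analysis is "to compare the degree of symptomatic improvement in the intervention group and the control group and to analyze the group × time interaction".
- "Binary Logistics regression and COX regression will be used to compare the changes in each indicator before and after the intervention between the two groups".
- The threshold throughout is that "relevant data will be considered statistically significant if P < 0.05". Sidedness is not stated.

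Table 1 (Participant timeline) shows ISI collected at screening, baseline (V1), day 35 (V2), and 6 and 12 months (V3, V4). Remitters and responders appear among the secondary indicators, but only as a number in the study group. All-cause dropout is an applicability indicator.

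**The concern.** Three things in the stated methods do not serve the success rule well.

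1. The test that fits the rule best, the independent-samples t-test, makes no use of baseline ISI, although V1 measures it in every patient. This costs precision that could be had for nothing.
2. The group × time analysis answers another question. With all four visits in the model, the interaction has 3 degrees of freedom and detects any difference in profile up to 12 months. It can be significant without a day-35 difference, and the reverse.
3. Logistic regression needs a binary outcome and Cox regression needs an event time. The changes to which the article assigns them are differences in continuous scores between fixed visits, with no cut-off, event or time origin given. As written, these models have no defined estimand.

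At stake are some power on the primary comparison, a clear statement of which result decides success, and results from two regressions that could not be interpreted.

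**Working it through.** **Inputs.** From Sample size: 60 control and 120 study patients, standardised effect d = 0.5, dropout 15%, alpha 0.05, power 0.80. Evaluable patients: 60 × 0.85 = 51 and 120 × 0.85 = 102. Assumed, because the article gives neither: the correlation r between baseline and day-35 ISI (0.3, 0.5, 0.7), and the ratio k of baseline SD to day-35 SD. The day-35 SD is set to 1 and tests are taken as two-sided.

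**The plan's own figure.** A two-sided comparison of means at d = 0.5 with 1:2 allocation needs (1.96 + 0.842)² × 1.5 / 0.25 = 47.1, so 48 control and 96 study patients. Dividing by 0.85 gives 57 + 114 = 171. The article's 180 is not reproduced exactly but is slightly larger, which is on the safe side. The two-proportion formula printed there cannot be run, since its rates and margin are not given.

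**Unadjusted t-test at day 35.** Noncentrality = 0.5 × √(51 × 102 / 153) = 0.5 × √34 = 2.915. Power = Φ(2.915 − 1.96) = 83%.

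**ANCOVA on baseline ISI.** The residual SD becomes √(1 − r²), so the noncentrality is 2.915 / √(1 − r²). This does not depend on k.

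| r | √(1 − r²) | noncentrality | ANCOVA power | t-test power |
|---|---|---|---|---|
| 0.3 | 0.954 | 3.056 | 86% | 83% |
| 0.5 | 0.866 | 3.367 | 92% | 83% |
| 0.7 | 0.714 | 4.082 | 98% | 83% |

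The exact noncentral-t values differ by half a percentage point at most.

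**Two-visit group × time test.** On V1 and V2 alone this equals a t-test on the change score, whose SD is √(1 + k² − 2rk). At r = 0.3:

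- k = 1: SD 1.183, power 69%.
- k = 0.7: SD 1.034, power 80%.
- k = 0.6: SD 1.000, power 83%, the same as the post-score t-test.

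The change score is less precise than the day-35 score only when r < k/2.

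**Type I error if either test could count.** Under the null, the t-test and change-score statistics have correlation (1 − rk) / √(1 + k² − 2rk). The chance that at least one exceeds ±1.96 is:

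- k = 1: 8.8%, 9.1% and 9.4% for r = 0.3, 0.5 and 0.7.
- k = 0.7: 8.0%, 8.2% and 8.3%.
- k = 0.6: 7.7%, 7.8% and 7.8%.

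Each test alone holds about 5%. In a simulation of 10,000 null trials per setting with 51 and 102 patients, a single pre-named ANCOVA had a type I error of 4.8–5.0%.

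**Logistic and Cox regression.** No arithmetic applies. The Statistical analysis section attaches them to changes in each indicator. Most of the indicators listed under Outcome measurements and instruments (ISI, HAMA, HAMD, PSQI, DBAS-16) are scores, and Table 1 has them taken at fixed visits.

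**The case against.** The unadjusted t-test is unbiased under randomisation, holds about 5% error, and at 83% exceeds the planned 80% power. At a low correlation such as 0.3, ANCOVA gains only about 3 percentage points. All of this stands: the t-test is not an error, and the case for ANCOVA is that it is better at no cost. An article may also leave covariates to a fuller document, so the missing covariate alone would be no finding. Here, however, the article has already chosen its methods.

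A reader might infer that the plan itself inflates the type I error, because four methods are applied to ISI and any of them could be reported. The text does not support that. It ties success to one contrast, the t-test fits that contrast most naturally, the ANOVA is introduced for a different question, and the regressions come as additions for the indicators generally.

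A reader might also infer that the interaction test must be weak, since entry at ISI of 15 or more truncates baseline and lowers its correlation with day 35. The 69% figure at r = 0.3 assumes equal SDs, and truncation also shrinks the baseline SD. At k of 0.6 to 0.7 the power is 80–83%, so no general loss follows.

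Finally, the trial does have outcomes that could suit logistic or Cox regression, such as response, remission and dropout. The fault is in the stated assignment to score changes, not in having these methods in the plan.

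**Conclusion.** The point holds as an improvement to the primary analysis and a correction of one misassigned pair of methods. Baseline-adjusted ANCOVA raises power from 83% to 86–98% over assumed correlations of 0.3 to 0.7, given 51 and 102 evaluable patients and d = 0.5. The four-visit interaction does not test the day-35 success criterion, and logistic and Cox regression should not be run on score changes.

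The error figure of roughly 8–9% is conditional. It applies only under a rule accepting either the t-test or the two-visit interaction, which the article neither states nor excludes. Neither the t-test nor the planned sample size is invalid.

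**What to change.** State one primary analysis: ANCOVA of day-35 (V2) ISI on arm and V1 ISI, reporting the adjusted mean difference with its 95% confidence interval, tested at two-sided P < 0.05. Success is then judged on this result alone. Keep the t-test and the repeated-measures ANOVA as supportive.

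Remove logistic and Cox regression from the comparison of score changes. Reserve them for binary or time-to-event outcomes such as response/remission or dropout. If response or remission is to be compared between arms, define the cut-off and count it in both arms, since the article now lists it for the study group only.

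The change concerns ISI. HAMA, HAMD and PSQI are specified as reduction rates, and moving them to the same score model would alter those endpoints, so it is not part of this fix.

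The cost is a few sentences in the analysis section, settled before unblinding. ISI is already collected at V1 and V2, and the named software fits ANCOVA.

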## Discussion

5

This online trial will test the effectiveness in terms of clinical outcomes and applicability of a self-help intervention platform to help alleviate insomnia combined with anxiety and/or depressive symptoms, a common clinical condition.

There are several limitations inherent in this study. Firstly, there is a possibility of dropout in either of the two groups. We will analyze and investigate the reasons for dropouts. Secondly, in terms of the applicability of this platform, older adults and patients with poor cognitive learning may have difficulty with self-help interventions, which in turn affects the validity and general applicability of this platform.

Thirdly, this self-help treatment relying on electronic technology may be more appealing to younger patients, who are more concerned with efficiency, time saving and personal privacy, and therefore prefer online interventions. Smart CBT-I plus lacks generalizability to different age groups.

Fourth, Smart CBT-I plus may be more suitable for patients with higher adherence and more positive psychological engagement, requiring more patient initiative, but it is not appealing to some patients with sleep disorders who have severe attention and energy deficits due to poor sleep and mood and who do not have sufficient motivation and conditions for active help-seeking.

This study also has several strengths. People with insomnia combined with depression and/or anxiety are a large group in China. In contrast, psychological resources and capacity to provide psychological interventions for this group are limited due to the shortage of qualified psychotherapeutic resources and the high cost of treatment. Therefore, it is particularly important to look for optimization techniques that use standardized procedures and produce positive results. Smart CBT-I plus can save costs such as time and economy, is more convenient and efficient, and has higher accessibility and applicability, which is the potential effects it has. Unlike previous mental health indicators involving the diagnosis of mental disorders such as insomnia, depression, anxiety, etc., this study chose symptoms rather than diagnostic criteria as inclusion criteria. Shifting from a disease-orientated intervention model to a health-orientated intervention model for accurate psychological self-help health interventions. These technologies have the potential to be further developed and made available to a wider population. At the same time, in the control group of this study, some popular science articles will be used to provide a mild intervention to the patients, and it will be verified what effect this will have and whether it has some value and significance.As a resource for non-stigmatizing and complementary psychological interventions that address, prevent, treat and promote mental health, these techniques are expected to have a sustainable positive impact on people’s mental healthcare and society at large.
